#### Initial classification

2.5.1

BCQ(+) is a questionnaire that is comprised of 19 questions with 1-to-5 rating scales, making the range of total score to be from 19 to 95 points with the cut-off score of 30.5 points for Yang-Xu.^[27]^ BCQ(−) is composed of another set of 19 questions with the same 5-point Likert scales, with the cut-off score of 29.5 points for Yin-Xu.^[26]^ BCQ(s) consists of 23 questions with the same Likert scale and cut-off score of 26.5 points for Stasis.^[28]^ A patient is diagnosed as Yang-Xu, Yin-Xu, and/or Stasis if his/her total score exceeds the corresponding cut-off score for each respective questionnaire. Therefore, patients will be categorized into 8 body constitutions of Yang-Xu, Yin-Xu&Yang-Xu, Yang-Xu & Stasis, Yin-Xu, Yin-Xu & Yang-Xu & Stasis, Yin-Xu & Stasis, Stasis, and Gentleness based on their BCQ scores.^[23,25]^

#### Classification used in this study

2.5.2

Yang-Xu or Yin-Xu constitution is shaped by the persisting decrease of Yang or Yin, so patients who correspond to either Yang-Xu or Yin-Xu (not mutually exclusive) will be classified into Xu (Deficiency) group. On the other hand, patients that are diagnosed as Stasis through BCQ(s) will be included in Stasis group since “Stasis” constitution is formed by the persistent disruption of the dynamic balance between Yin and Yang.^[26–28]^ Patients who belong to none of the 3 body constitutions (Yang-Xu or Yin-Xu, Stasis) will be classified into the Gentleness group^[23,25]^. Therefore, the 8 body constitution types will be regrouped into 3 pattern identification types, Xu, Stasis, and Gentleness.

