#### Sample groups on LCE groups

2.6.3

All the lung cancer patients will be divided into 3 LCE groups according to their pattern identification types (Xu, Stasis, or Gentleness). The patients who will be assessed as Xu will belong to lung cancer entire Xu (LCEX) group. Likewise, the patients who will be assessed as Stasis will be included to lung cancer entire Stasis (LCES) group, while patients to be assessed as Gentleness will belong to lung cancer entire Gentleness (LCEG) group.

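### The Xu and Stasis rules in section 2.5.2 overlap: three of the eight constitutions meet both, so the regrouping does not give the three separate groups the protocol says it gives

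*Protocol article*

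**What the plan says.** All references are to the protocol article.

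- **Section 2.5.1 (Initial classification)** allows the three diagnoses in any combination: "A patient is diagnosed as Yang-Xu, Yin-Xu, and/or Stasis if his/her total score exceeds the corresponding cut-off score for each respective questionnaire". It lists the resulting types as "Yang-Xu, Yin-Xu&Yang-Xu, Yang-Xu & Stasis, Yin-Xu, Yin-Xu & Yang-Xu & Stasis, Yin-Xu & Stasis, Stasis, and Gentleness".
- **Section 2.5.2 (Classification used in this study)** gives three rules. For Xu: "patients who correspond to either Yang-Xu or Yin-Xu (not mutually exclusive) will be classified into Xu (Deficiency) group". For Stasis: "patients that are diagnosed as Stasis through BCQ(s) will be included in Stasis group". For Gentleness: "Patients who belong to none of the 3 body constitutions (Yang-Xu or Yin-Xu, Stasis) will be classified into the Gentleness group". It concludes that "the 8 body constitution types will be regrouped into 3 pattern identification types, Xu, Stasis, and Gentleness".
- **Section 2.6.3 (Sample groups on LCE groups)** says "All the lung cancer patients will be divided into 3 LCE groups according to their pattern identification types". It then repeats the Xu and Stasis assignments and gives neither precedence.
- **Section 2.7.3** draws the LCR groups from the LCE groups.
- **Section 2.9** pools plasma physically by group, giving six pools.
- **Section 2.13** compares the pools. Comparisons (4) and (5) list the glycoproteins unique to, or shared among, the three pattern groups, in LCE and in LCR respectively.

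**The concern.** The pattern group is the exposure in this study, and the lists of unique and shared glycoproteins are its main result. Those lists can be interpreted only if each patient belongs to one known group. The Xu rule sets no condition on Stasis, and the Stasis rule sets none on Xu. The parenthesis about not being mutually exclusive qualifies Yang-Xu against Yin-Xu. It says nothing about Xu against Stasis.

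If the rules are applied as written, one patient's plasma goes into two pools that are then contrasted. Shared plasma favours finding the same proteins in both, so it fills the intersection set and thins the unique sets. The LCR groups can inherit the overlap. Matching on control factors does not remove it, since a patient eligible for both groups matches himself or herself exactly.

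If the groups are meant to be disjoint, three of the eight types have no stated destination, and the content of the Xu and Stasis pools depends on a choice the protocol does not record.

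**Working it through.** **Inputs.** Three binary diagnoses, Yang-Xu, Yin-Xu and Stasis, in any combination (section 2.5.1). The three grouping rules are those of section 2.5.2.

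**Step 1: reproduce the protocol's count.** Three yes/no diagnoses give 2 × 2 × 2 = 8 types, as stated.

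**Step 2: apply the rules to each type.**

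| Type | Xu rule | Stasis rule | Gentleness rule |
|---|---|---|---|
| Yang-Xu | yes | no | no |
| Yin-Xu | yes | no | no |
| Yin-Xu & Yang-Xu | yes | no | no |
| Yang-Xu & Stasis | yes | yes | no |
| Yin-Xu & Stasis | yes | yes | no |
| Yin-Xu & Yang-Xu & Stasis | yes | yes | no |
| Stasis | no | yes | no |
| Gentleness | no | no | yes |
| Total | 6 | 4 | 1 |

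Memberships: 6 + 4 + 1 = 11 for 8 types. The excess, 11 − 8 = 3, is the three types that meet both Xu and Stasis. They are 3 of the 6 Xu types and 3 of the 4 Stasis types.

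**Step 3: what a disjoint rule would give.** Number of types in Xu / Stasis / Gentleness:

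- mixed types to Stasis only: 3 / 4 / 1;
- mixed types to Xu only: 6 / 1 / 1;
- mixed types kept apart: 3 / 1 / 1, with 3 in a separate group.

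Each choice gives a different Xu pool, a different Stasis pool, or both. The visible text does not choose.

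**Step 4: how many patients could be affected.** The protocol plans 100 participants (section 2.8) and gives no prevalences, so the prevalences below are assumptions. If a fraction p meets Xu and the same fraction meets Stasis, independence gives 100 × p × p mixed patients. Without independence, the number lies between 100 × max(0, 2p − 1) and 100 × p. The pure count in each of Xu and Stasis is 100 × p minus the mixed count.

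| Assumed p | Mixed, independence | Possible range | Pure Xu, and pure Stasis, independence | Mixed share of each pool on the literal reading |
|---|---|---|---|---|
| 0.30 | 9 | 0 to 30 | 30 − 9 = 21 | 9/30 = 30% |
| 0.50 | 25 | 0 to 50 | 50 − 25 = 25 | 25/50 = 50% |
| 0.70 | 49 | 40 to 70 | 70 − 49 = 21 | 49/70 = 70% |

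At the upper end of each range, no pure Xu or pure Stasis patients remain.

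**Step 5: are mixed types likely to be rare?** The text gives no reason to assume so. BCQ(s) has 23 items scored from 1, so its floor is 23 and its cut-off is 26.5. One item rated 5 with the other 22 rated 1 gives 22 + 5 = 27, which is above the cut-off. This shows that the Stasis threshold lies close to the floor; it does not estimate a prevalence.

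**The case against.** The best defence is that three disjoint groups were clearly intended. Regrouping eight types into three and dividing all patients both point that way. Section 2.5.2 introduces Stasis as a contrast to Xu and describes it as a disturbed balance between Yin and Yang, so a reader could take Stasis to override Xu. That would give the 3 / 4 / 1 split. Figure 1, the methodology flow chart, is not shown and might contain the rule. The study is also preliminary and non-interventional.

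Much of this stands as to intent, but it does not supply the rule. No visible sentence says that Stasis overrides Xu, and no visible text refers to an allocation rule in a figure. The article gives the classification its own section, and the rules stated there do not produce the result stated there.

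The defence does block several stronger readings that a reader might infer:

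- **That plasma will certainly be pooled twice.** This is one of two readings. The other is disjoint groups with an unstated allocation.
- **That every protein from a mixed patient drops out of the unique lists.** Identification in a pool depends on dilution and on the confidence and score thresholds of section 2.13.
- **That the loss can be expressed as a shrunken difference or a correlation between pool means.** The planned readout is lists of identified proteins, and the patient split is unknown.
- **That groups would be fixed after the results are seen.** The questionnaire comes first, and pooling precedes mass spectrometry, so even an improvised placement would precede the proteomic data.
- **That mixed patients should simply be left out.** This conflicts with the aim in sections 2.6.2 and 2.6.3 of analysing all patients, and it could leave a group below the minimum of 10 in section 2.8.1.

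**Conclusion.** The point holds as a contradiction in the classification rule. Sections 2.5.2 and 2.6.3 promise three separate groups, but the rules assign three of eight types to both Xu and Stasis, and no visible text resolves it. That count needs no assumption.

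On the literal reading, shared plasma biases comparisons (4) and (5) towards overlap. On the disjoint reading, the composition of the Xu and Stasis pools is undefined. How much this matters depends on the share of mixed patients. With 100 participants and the assumed prevalences above, independence gives 9 to 49 mixed patients, and the range without independence runs from 0 to 70. These figures illustrate and do not predict. Three of eight categories is likewise not a share of patients.

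It should be corrected before pooling, because a physical pool cannot be unmixed, whereas correcting the rule beforehand takes only wording and a re-sort of questionnaire scores.

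**What to change.** Before any plasma is pooled:

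1. Reconcile sections 2.5.2 and 2.6.3 with one explicit table that assigns each of the eight types to exactly one group, and use the same table for LCR selection.
2. Tabulate the number of patients in each of the eight types.
3. Preferably, place the three mixed types in a fourth pool of their own. All patients are then still analysed, and the Xu and Stasis pools neither share patients nor blend patterns. The three-group wording must change to match.
4. If the counts would leave a pure group below the minimum of 10, assign the mixed types to one named group by a fixed rule, and describe that group as including mixed types wherever its results are reported.

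**Cost.** The rewording and re-sort use questionnaire scores the study collects anyway. A fourth pool adds at least two mass spectrometry runs and, with two search programs, at least 2 × 2 = 4 data files, and it makes the Xu and Stasis pools smaller than on the literal reading. The fallback needs no extra pool but leaves one group less pure.

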### Lung cancer entire (LCE) groups

2.6

#### Clinical information

2.6.1

Lung cancer patients will be interviewed face-to-face for 19 categories of clinical information, including sex, age, race, body weight, body height, disease history (cancer, diabetes, angina/myocardial infarction, and hypertension), surgical history, family history, medication history, smoking, alcohol, and cancer diagnostic information (diagnosis, surgery type, clinical TNM stage, pathological TNM stage, and cancer subtypes).

#### Holistic viewpoint

2.6.2

Lung cancer patients will be randomly recruited without any prior categorization of their body constitutions. A disease of a patient with a certain type of pattern identification may be considered as arising from the patient's body constitution. Thus, it is important to holistically analyze all the lung cancer samples according to their pattern identification types.

#### Sample groups on LCE groups

2.6.3

All the lung cancer patients will be divided into 3 LCE groups according to their pattern identification types (Xu, Stasis, or Gentleness). The patients who will be assessed as Xu will belong to lung cancer entire Xu (LCEX) group. Likewise, the patients who will be assessed as Stasis will be included to lung cancer entire Stasis (LCES) group, while patients to be assessed as Gentleness will belong to lung cancer entire Gentleness (LCEG) group.

### Lung cancer representative (LCR) groups

2.7

#### Definition of representative sample

2.7.1

Sampling is particularly crucial when heterogeneous materials are analyzed. It is critical that the analysis aims are clearly declared and that an appropriate sampling procedure is adopted. In some situations, a sampling strategy needs to be devised in order to optimize the value of the analytical information collected. A representative sample is what truly reflects the composition of the material to be analyzed within the context of a defined analytical problem.^[42]^

#### Control factors

2.7.2

Glycoproteins in blood can vary qualitatively and quantitatively by numerous variables such as sex, age, and medical history. The glycoproteins must be qualitatively and quantitatively analyzed based on the pattern identification of the lung cancer patients. We hypothesize that each pattern identification of TKM as well as other variables such as sex, age, medical history, and etc. affects glycosylations on plasma proteins. Therefore, all the other variables other than pattern identification must be strictly controlled.

Since it is impossible to control all of the 19 variables of clinical information, we need to select as many variables as possible that are within our control. For example, smoking can be selected as the control factor that is closely related to lung cancer while sex ratio and average age can be considered as basic control factors for qualitative and quantitative analysis of glycoproteins. Both TNM stage and cancer subtype can be selected as control factors. Disease histories can be selected as control factors that can affect glycosylation in cancer plasma. Patients with no prior history of cancers other than lung cancer will be selected because other cancers may affect the aberration in the glycan moieties of glycoproteins in the plasma. Cancer histories from direct family can be considered as a genetic factor.

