(1)the glycoprotein comparison sets from the first and second MS/MS runs for the confirmation of reproducibility(2)the glycoprotein comparison sets from the 2 protein search engines to increase the confidence level of identified proteins(3)the glycoprotein comparison sets between LCE groups and LCR groups to check the representativeness(4)the unique and intersection glycoproteins set by comparison of LCE groups (LCEX, LCES, and LCEG) based on their pattern identifications assessed from BCQs of the lung cancer patients(5)the unique and intersection glycoproteins set by comparison of LCR groups (LCRX, LCRS, and LCRG) based on their pattern identifications assessed from BCQs of the lung cancer patients.

The overall data processing and analysis procedures are described in Figure 2. Unique glycoproteins from each group with each pattern identification of lung cancer patients will be generated from the results.

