## Discussion

3

This is the first study in Korea to diagnose pattern identification with BCQ assessment which was proven to obtain validity and reliability in Taiwan^[39–40]^ and Hong Kong^[41]^. This study is also the first to apply BCQ assessment to lung cancer patients. Furthermore, this is the first to correlate BCQ and patients’ blood through glycoproteomics. After diagnosis of pattern identification type with BCQ, glycoproteomics approach will be introduced to all the plasma in order to establish scientific and biomedical criteria on BCQ for the first time. Two sets of patients’ plasma will be explored from each pattern identification type of TKM; a holistic evaluation (LCE groups) and a scientific validation of the representativeness (LCR groups). It is regarded that the diseases of a patient with specific pattern identification arise from the corresponding pattern identification. Thus, it is important to holistically analyze the entire lung cancer patients according to their pattern identification types. On the other hand, by carefully selecting appropriate control factors, all the control factors other than the pattern identification are prevented from interfering with the change in glycoproteins in their blood. This change may vary depending on diverse variables such as sex, age, and medical history.

The patient-optimized TKM for lung cancer can be applied to cancer therapy for future clinical trials and treatments by presenting scientifically valid criteria on patient's pattern identification from this trial. The identified plasma proteins from each pattern identification type will be categorized as pattern identification indicators (biomarkers) for precision medicine. In the long run, these proteins can also be utilized as lung cancer biomarkers aiming for development of in vitro lung cancer diagnostic kits based on pattern identification of lung cancer patients.

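### Unique glycoproteins from the uncontrolled LCE pools can be reported as pattern indicators, because the LCE–LCR check tests whether LCR represents LCE and gives no rule for proteins on which they disagree

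*Protocol article*

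**What the plan says.** All places are in the protocol article.

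- **Premise (2.7.2, Control factors).** The investigators hypothesize that pattern type matters for glycosylation, and also that "other variables such as sex, age, medical history, and etc. affects glycosylations on plasma proteins". From this they conclude that "all the other variables other than pattern identification must be strictly controlled". The next paragraph qualifies this: "Since it is impossible to control all of the 19 variables of clinical information, we need to select as many variables as possible".
- **LCE groups (2.6.2, 2.6.3).** All patients are split by pattern type only. The stated reason is a holistic view of the whole sample.
- **LCR groups (2.7.3).** These are subsets of the LCE groups, chosen so that the numbers in each control factor are equal across pattern types.
- **Pooling (2.9).** Plasma is combined into six pools, one for each LCE and LCR group.
- **Analyses (2.13).** Comparison (3) sets LCE against LCR to check representativeness. Comparisons (4) and (5) derive unique and shared glycoproteins within the LCE set and within the LCR set, in matching words. The output is then described: "Unique glycoproteins from each group with each pattern identification of lung cancer patients will be generated from the results".
- **Validation (2.7.4).** Comparing LCE with LCR within a pattern type is meant to show whether LCR represents LCE, and this is to serve as validation of the unique proteins.
- **Use (Discussion).** "The identified plasma proteins from each pattern identification type will be categorized as pattern identification indicators (biomarkers) for precision medicine".

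**The concern.** By the plan's own premise, a difference between LCE pools may come from sex, age, smoking, stage, subtype or medical history and not from the pattern. Comparison (4) still produces a list of pattern-unique proteins from those pools, and the sentence that turns proteins into indicators does not separate that list from the one produced by comparison (5).

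The difficulty cannot be repaired at the analysis stage. Each group is measured as one pool, so the proteomic data carry no patient-level covariates to adjust for. Protection has to come from a rule for interpreting the lists. The rule that exists, representativeness, takes the uncontrolled set as its reference. At stake is whether a protein that tracks smoking or stage is reported as a marker of Xu, Stasis or Gentleness.

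**Working it through.** The plan gives no figure to reproduce: 100 participants (2.8) and at least 10 per LCE group (2.8.1) are stated without a calculation. The main check is a reading of the sections side by side.

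**1. What the check in 2.7.4 and comparison (3) can do.**

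| Protein is unique in | Reading under the plan's criterion | What it says about confounding |
|---|---|---|
| LCE and LCR | LCR represents LCE; protein validated | Not independent evidence, since LCR patients are also in the LCE pool |
| LCE only | LCR fails to represent LCE | May be confounding removed by matching, which is the purpose of LCR; also possible by chance or from the smaller pool |
| LCR only | LCR fails to represent LCE | May be a pattern difference masked in LCE, or chance |

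The second row is the critical one. The criterion does not count against the protein there, and no consequence for a discordant protein is stated.

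**2. Direction of bias (assumed figures; the documents give none).** Take a protein found in 10% of smokers and in no non-smokers, unrelated to pattern. Pools hold 20 patients, and one carrier is enough for detection. With smoker share s, P(present) = 1 − (1 − 0.1s)^20.

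- s = 0.7: 1 − 0.93^20 = 0.766
- s = 0.2: 1 − 0.98^20 = 0.332
- s = 0.5: 1 − 0.95^20 = 0.642

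Two pools, 70% against 20% smokers:
- unique to the first: 0.766 × (1 − 0.332) = 0.51
- unique to the second: 0.332 × (1 − 0.766) = 0.08
- total: 0.59

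Two pools, 50% each: 0.642 × (1 − 0.642) = 0.23 for each pool, total 0.46.

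The plan has three pools. Adding a third of 20 with 50% smokers multiplies the first two results by 1 − 0.642 = 0.358, giving 0.18 and 0.03. Uniqueness to the third pool is 0.642 × 0.234 × 0.668 = 0.10, so the total is 0.31. With all three at 50% the total is 3 × 0.642 × 0.358² = 0.25.

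Imbalance therefore mainly decides which pool the protein is credited to. It adds 0.13 (two pools) or about 0.06 (three pools) to the total chance of spurious uniqueness.

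**3. How easily LCE pools become unbalanced by chance alone.** Let a binary covariate be unrelated to pattern, with assumed prevalence 20% to 50%. Exact binomial probabilities are summed over all outcomes in which the highest and lowest group proportions differ by at least 30 points.

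| LCE sizes | Probability |
|---|---|
| 33/33/34 | 0.01 to 0.04 |
| 10/45/45 | 0.05 to 0.14 |
| 10/10/80 | 0.17 to 0.31 |

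The last row is the most unequal split allowed (100 − 2 × 10 = 80). A real association between a covariate and pattern type would add to these values; the documents neither report nor exclude one.

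**The case against.** A reader might infer that the LCE comparison breaks the plan's own rule. The text does not support that. The sentence on strict control stands in section 2.7, which concerns the LCR groups; the following paragraph concedes that full control is impossible; and the LCE set is uncontrolled openly, for a stated reason.

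A reader might also infer that the two comparisons have equal standing throughout. They do not: 2.7.4, comparison (3) and the Discussion give LCR a validating role. That role is real, but for the reasons in step 1 of the working it does not screen out confounded proteins.

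Other counter-arguments:

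- **The missing rule may be in a fuller document.** It may be. However, the article itself fixes the purpose of the LCE–LCR comparison as representativeness and words the indicator sentence without restriction. The point rests on those statements, not on omitted detail.
- **The smoking example weakens the remedy.** This stands in part. Balanced pools still give a total of 0.46 in the two-pool version, so restricting claims to LCR removes imbalance in the selected factors but not chance uniqueness between single pools. The example is one assumed scenario.
- **LCE membership may be narrower than it appears.** Blood is drawn before surgery, and the eligibility table is not visible. That LCE may include patients with other prior cancers is inferred from 2.7.2, which selects such patients out for LCR as a separate step.
- **The study is preliminary.** It is, and biomarker discovery in a large population is listed as a long-term outcome (2.2.2). This limits the consequence, but the Discussion still calls the present study's proteins indicators.

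**Conclusion.** The point holds as a gap in interpretation. The plan regards other variables as affecting glycosylation, controls selected ones only in LCR, derives unique proteins from both sets in matching terms, and does not confine indicator claims to LCR. The validating comparison runs in a direction that would excuse a confounded LCE protein, and overlap between the sets means that agreement is weak support.

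The size cannot be estimated from the documents. The smoking calculation shows only the direction of bias under assumed detection rates, smoking shares and pool sizes. Chance imbalance of 30 points is unlikely with near-equal groups (0.01 to 0.04) and material only when groups are very unequal (0.17 to 0.31 at 10/10/80). No stated figure in the plan changes. The wording should be corrected; the design need not be.

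**What to change.** In 2.7.4 and 2.13, and in the matching Discussion sentence:

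1. State that pattern-specific (indicator) claims rest on the LCR comparison (5).
2. Keep the LCE comparison (4) as descriptive.
3. Label a protein that is unique in LCE but not in LCR as unadjusted and possibly confounded, and do not call it a pattern indicator.
4. Tabulate sex, age, smoking, stage, subtype and prior cancer for each LCE pool beside its protein list, from the clinical items already collected under 2.6.1.

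The cost is a few sentences and one descriptive table; no new samples or assays are needed, and the holistic analysis stays. The downside is a shorter list of claimed markers, drawn from smaller pools. The change does not deal with chance uniqueness between single pools, so the LCR list should still be presented as exploratory.
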